### Outcomes

We will examine the efficacy of pregabalin on postoperative pain using the variables described in the literature [12]. The primary outcomes are pain intensity measured on a visual analogue scale (VAS) (length, mm), total administered amount of IV PCA measured (volume, mL), and frequency of rescue analgesics administered (the number of administrations, according to the type of rescue analgesic, and the total amount of morphine equivalent dose). The VAS score is evaluated using a pain ruler marked from 0 (no pain) to 100 (maximal pain) mm, with patients directly indicating their pain level. The secondary variables are the incidence and frequency of nausea and vomiting caused by IV PCA. Assessments of all variables will be performed during the first 72 h following the arrival of the participant at the general ward, subdivided into four periods: 1–6 h, 6–24 h, 24–48 h, and 48–72 h. We will evaluate pain between the midpoint and the end of each of the four time zones, aiming to measure as close to the end time as possible and use the pain scores at all four time points as the primary outcome. The pain levels in each time zone will be compared to see if they differ depending on the treatment method. Through this, we will ascertain how the treatment effect changes over time and how these changes differ among different treatment groups. Through these variables, we plan to check the effects of pregabalin on reduction of postoperative pain and IV PCA usage. In addition, we will examine whether reduction of IV PCA usage has a beneficial effect on the patient by reducing the incidences of common side effects, nausea and vomiting.

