## Statistical methods

### Statistical methods for primary and secondary outcomes

The primary objective of this study is to compare the effect of different doses of pregabalin to placebo on pain relief and the need for additional analgesics during the 72-h period following surgery, at various time points. Additionally, the study aims to assess the incidence of adverse events during this period. Primary outcomes include the VAS pain score, total dose of IV PCA administered, and frequency of rescue analgesic administered. We will use the Kolmogorov–Smirnov test (K-S test) to assess the normality of the primary outcome measure. If the normality assumption is met, we will perform an analysis of variance (ANOVA) analysis; otherwise, we will use the Kruskal–Wallis test for comparison. We will use the Bonferroni’s method for conducting subgroup analysis to account for multiple comparisons. Categorical variables, such as the incidence and frequency of nausea and vomiting caused by IV PCA or the incidence of side effects (sedation, dizziness, headache, visual disturbance, and swelling), will be compared between the groups using the chi-squared test. Statistical analyses will be performed using SPSS 20.0 (IBM, Armonk, NY, USA). In all analyses, *P* < 0.05 will be taken to indicate statistical significance.

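### The protocol says that comparing arms within each period will show how the treatment effect changes over time, but no planned test has a time factor or arm-by-period term.

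*Protocol article*

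**What the plan says.** All the relevant text is in the protocol article.

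- **Outcomes, measurements.** Assessments cover the first 72 hours on the ward, "subdivided into four periods: 1–6 h, 6–24 h, 24–48 h, and 48–72 h". Each patient gives one VAS score per period, and the investigators will "use the pain scores at all four time points as the primary outcome".
- **Outcomes, method and aim.** "The pain levels in each time zone will be compared to see if they differ depending on the treatment method". The next sentence presents this comparison as the means by which the trial will "ascertain how the treatment effect changes over time and how these changes differ among different treatment groups".
- **Statistical methods for primary and secondary outcomes.** After a Kolmogorov–Smirnov check: "If the normality assumption is met, we will perform an analysis of variance (ANOVA) analysis"; "otherwise, we will use the Kruskal–Wallis test for comparison". Multiplicity is handled by Bonferroni's "method for conducting subgroup analysis to account for multiple comparisons". No repeated-measures term, time factor or interaction is named.
- **Methods for additional analyses.** None is planned.
- **Sequence generation.** Randomization is stratified by sex and by age (under 65 versus 65 and over).

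**The concern.** Whether a treatment effect changes over time, and whether that change differs by dose, is a question about the arm-by-period interaction. It needs a comparison of effects between periods that allows for the correlation of scores within a patient. A set of between-arm tests, one per period, contains no such comparison. One period can fall below P = 0.05 and the next above it although the effect is the same in both.

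At stake is the reading of the time course. If the sentence in Outcomes is followed, a result that is significant at 6–24 h and not at 48–72 h could be reported as an effect that wears off. Conversely, a real change over time would have no test of its own.

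**Working it through.** **1. The plan's own calculation.** The Sample size section gives f = 0.448, alpha = 0.0167, power 0.95 and four groups. With the noncentral F distribution for a one-way ANOVA (noncentrality N × f², 3 and N − 4 degrees of freedom), the smallest balanced N is 112, with power 0.955. This reproduces the stated 112, or 28 per group. Then 28 / 0.85 = 32.9, so 33 per group and 132 in total. The calculation is for a one-way comparison of a single PCA value per patient. It does not size any arm-by-period question.

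**2. The stated aim against the stated tests.**

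| Element | Aim in Outcomes | Tests in Statistical methods |
|---|---|---|
| Between arms | yes | yes (ANOVA or Kruskal–Wallis) |
| Time factor | required | not named |
| Arm-by-period term | required | not named |
| Within-patient correlation | required | not named |

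**3. How often separate tests mislead.** The documents give no VAS effect size and no within-patient correlation, so both are assumed. The simulation used 4 arms × 28 patients × 4 periods, unit SD, equal correlation rho between periods, evenly spaced arm means and 4,000 runs per setting. It compared four one-way ANOVAs at 0.05 with an arm-by-period F test on 9 and 3 × (112 − 4) = 324 degrees of freedom.

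*Effect constant over time:*

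| rho | f = 0.25: some but not all periods significant | f = 0.30: same | Arm-by-period test rejects (f = 0.25) |
|---|---|---|---|
| 0.3 | 74% | 59% | 5.3% |
| 0.5 | 62% | 48% | 5.9% |
| 0.7 | 49% | 38% | 6.1% |

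Hand check: at f = 0.25, N = 112 and alpha = 0.05, a single period has power 0.572. If the periods were independent (rho = 0), the chance of a mixed pattern would be 1 − 0.572⁴ − 0.428⁴ = 1 − 0.107 − 0.034 = 0.86. The simulated values fall below this as rho rises, as they should.

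*Effect fading in roughly equal steps from f = 0.4 in the first period to 0 in the last:* the arm-by-period test rejects in 74%, 90% and 99% of trials for rho = 0.3, 0.5 and 0.7. The stated plan has no corresponding test.

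**4. Precision from pooling.** The variance of the mean of four equally correlated scores, relative to one score, is (1 + 3 × rho) / 4 = 0.475, 0.625 and 0.775. Standard errors are therefore 31%, 21% and 12% smaller. With a constant f = 0.25, power for the average effect is 90%, 80% and 70%, against 57% for one period. This is a separate efficiency point and does not measure the interaction problem.

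**The case against.** The best defence has three parts. First, change over time is not the primary objective: Statistical methods states that as a comparison of doses with placebo at various time points over 72 hours, and separate between-arm tests are valid for it. This stands, and it limits how serious the point is. Second, ANOVA is not described as one-way, the article is condensed, and a fuller analysis plan might define a repeated-measures ANOVA. This carries little weight. Outcomes itself names comparison within each time zone as the route to the conclusion, and the Kruskal–Wallis alternative compares independent groups with no time factor, so on that branch the aim cannot be met on any reading. Third, the protocol nowhere says that it will read mixed significance as a time pattern. That is true. It says only that the per-period comparisons will reveal the change, and it offers no other basis for judging it.

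A reader might infer more than the text supports:

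- **That per-period testing forces exclusion of patients with a missing score.** It does not. The exclusion is a separate rule in the section on non-adherence and missing data.
- **That unequal period lengths bias the comparisons.** Within a period, all arms share the same length.
- **That rescue counts will simply be put through ANOVA.** Outcomes that fail the normality check go to Kruskal–Wallis.
- **That no 72-hour effect is estimated at all.** Total PCA dose is a named primary outcome, and the Abstract frames it over 72 hours.
- **That a mixed model reduces everything to one test.** It still yields three dose-versus-placebo contrasts, an interaction test and period estimates.
- **That pooling always helps.** A fading effect is diluted by averaging: in the fading scenario, the test of the average had power 72%, 58% and 48% as rho rose.

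**Conclusion.** The point holds as a mismatch between one stated aim and the stated tests: the planned analysis cannot support a conclusion about how the treatment effect changes over time or how that change differs by arm. The per-period tests are not invalid, and the comparison of doses with placebo is not undermined.

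Under a constant effect of f = 0.25 with 28 per arm, period-by-period significance gives a mixed picture in roughly half to three quarters of trials; at f = 0.30 the range is 38% to 59%. These figures depend on the assumed effect size and equal correlation of 0.3 to 0.7. The logical gap does not depend on them.

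**What to change.** For VAS, prespecify one mixed model for repeated measures with arm, period, arm-by-period and the stratification factors (sex, age group), and a covariance structure named in advance.

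- Base any statement about change over time on the arm-by-period test.
- Report the 72-hour average and the per-period estimates for each dose against placebo, with confidence intervals.
- Drop the Kolmogorov–Smirnov gate for this outcome. Applied per period, it could switch between a comparison of means and one of ranks, so that periods would not be comparable.

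If this is not wanted, delete the change-over-time claim from Outcomes and confine conclusions to each period's own comparison.

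The cost is revised wording, modest extra analysis work and reliance on a model. The data and strata are already collected. The gain in precision depends on a correlation that the documents do not give. If partly observed patients are to contribute, the rule that excludes patients with missing data must be changed as well; the model alone does not do that.

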### Participant timeline

The participant timeline is shown in Fig. 1.

**Fig. 1 Fig1:**
[figure not shown]
Schematic diagram showing the timeline for key procedures

### Sample size

The prior calculation of the sample size indicated that at least 28 subjects were required for each group. For calculation, the software G*Power 3.1.9.7 was used with a statistical power of 0.95 at an effect size of 0.448 with an alpha level of 0.0167. The effect size was determined based on a previous study [18]. In this study, three groups—those treated with placebo, pregabalin 75 mg, and pregabalin 150 mg—each comprised 28 participants. The groups were compared based on their PCA usage, with mean values of 95.3, 96.6, and 105.2 respectively, and an approximate standard deviation of 10. For the purposes of this study, which involves four instead of three groups, a fourth hypothetical group was considered with the mean value of 96.6, which is the median value of the three established groups. Based on this data, Cohen’s *f* was calculated, resulting in an effect size of 0.448. To compare the four groups through Bonferroni’s test, the alpha level was set at 0.05 divided by 4, which is 0.0167. When calculated based on these parameters, the total sample size needed is found to be 112, and the number of participants needed per group is 28. Considering a follow-up loss of approximately 15%, 33 participants per group would be required, resulting in a total of 132 participants needed for the study.

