### Relevant concomitant care permitted or prohibited during the trial

After the surgical procedure, IV PCA (PS-1000; Unimedics, Seoul, Korea) will be administered and continued for 72 h. The PCA regimen will consist of fentanyl 1500 μg (total volume including saline: 150 mL) and will be administered at 2 mL/h as background infusion and 2 mL on demand with a 30-min lockout.

Concomitant therapy for comorbidities, such as hypertension, diabetes, rheumatoid arthritis, etc., will be permitted and documented. Any analgesic use is prohibited from 48 h before surgery until 72 h after surgery. If the participant asks for additional pain control, rescue analgesics, including oxycodone (IRcodon tab 5 mg; Unimed, Seoul, Korea), fentanyl patch (Durogesic patch 12 μg/h; Janssen Korea, Seoul, Korea), or pethidine (Pethidine 25 mg injection; Hana Pharm Co., Seoul, Korea), will be administered.

If participants present with nausea or vomiting, ramosetron (Nasea Injection 0.3 mg/2 ml; Daiichi Sankyo, Seoul, Korea) will be administered intravenously. If symptoms continue after ramosetron administration, metoclopramide (Macperan Injection 10 mg/2 ml; Dong Wha Pharm Co., Seoul, Korea) will be administered intravenously.

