The adverse effects of postoperative pregabalin have not been investigated in detail. Most studies focused on the efficacy and side effects of pregabalin when used preoperatively [25, 27]. Kim et al. [18] reported the incidence of pregabalin side effects until 48 h postoperatively, but the doses of pregabalin used in that study were 75 mg and 150 mg. Our study will focus on the efficacy and adverse effects of postoperative pregabalin at lower doses (25 mg, 50 mg, and 75 mg).

In conclusion, our study will provide evidence on the efficacy of pregabalin for postoperative pain relief after spinal surgery without major side effects even when used at the low dose of 25 mg.

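### The 0.95 power is derived from PCA-usage figures that cannot be 72 h volumes under this trial's own pump regimen, so it is unsupported for the 72 h PCA outcome

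*Protocol article*

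**What the plan says.** All references are to the protocol article.

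- **Sample size.** The planning data come from a cited three-arm study (placebo, pregabalin 75 mg and 150 mg). The section reports: "The groups were compared based on their PCA usage, with mean values of 95.3, 96.6, and 105.2 respectively, and an approximate standard deviation of 10". To reach four arms, "a fourth hypothetical group was considered with the mean value of 96.6". These inputs are said to give Cohen's f = 0.448, and the calculation uses "a statistical power of 0.95 at an effect size of 0.448 with an alpha level of 0.0167". The result is 28 evaluable per group (112 in total), raised to 33 per group (132) for about 15% loss. Neither the unit of PCA usage nor the period over which it was counted is stated.
- **Outcomes.** One of three primary outcomes is the "total administered amount of IV PCA measured (volume, mL"), assessed over the first 72 h on the general ward and split into 1–6, 6–24, 24–48 and 48–72 h.
- **Relevant concomitant care.** PCA is continued for 72 h from a total volume of 150 mL and "will be administered at 2 mL/h as background infusion and 2 mL on demand with a 30-min lockout".
- **Discussion.** The only time window given for the source study concerns harms: it "reported the incidence of pregabalin side effects until 48 h postoperatively, but the doses of pregabalin used in that study were 75 mg and 150" (both in mg).

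**The concern.** The planning means are around 100 with an SD of about 10. If they are mL, they are too low to be 72 h totals under the regimen that this protocol prescribes. If they are not mL, they are not this trial's outcome. Either way, the variability and group differences behind f were observed on something other than the 72 h volume, and the protocol offers no conversion or argument for using them.

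This is the only power statement in the article. A 72 h PCA result that shows no difference would be read as coming from a comparison with 95% power, although no figure in the document supports that for this outcome.

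**Working it through.** **1. The plan's own figure.** One-way ANOVA, k = 4 groups, N = 112, f = 0.448, alpha = 0.0167. Noncentrality = f² × N = 0.448² × 112 = 22.5. The noncentral F distribution with 3 and 108 degrees of freedom gives power 0.955, and 28 per group is the smallest n that reaches 0.95. Then 28 / 0.85 = 32.9, rounded up to 33 per group, 132 in total. Given f, the stated N and power reproduce. The question is whether f belongs to this outcome.

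**2. Lowest 72 h volume under the regimen as written.** Background rate × hours:

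- 72 h: 2 × 72 = 144 mL
- hours 1–72: 2 × 71 = 142 mL
- 48 h, for comparison: 2 × 48 = 96 mL

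Demand boluses can only add to these.

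**3. Comparison with the planning means.**

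| Planning mean | Below 144 mL by | Below 142 mL by |
|---|---|---|
| 95.3 | 48.7 | 46.7 |
| 96.6 | 47.4 | 45.4 |
| 105.2 | 38.8 | 36.8 |

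None can be a mean 72 h total in mL with the pump run as written. The two lower means lie close to the 48 h background of 96 mL. That makes a 48 h window plausible, but it is an assumption: the 48 h in the Discussion refers to side effects, not to PCA usage.

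**4. The 150 mL volume.** The document does not say whether the pump is refilled. Assuming no refill, a full 72 h total can only lie between 144 and 150 mL, which leaves 6 mL, or three boluses, above background. The largest possible difference between group means is then 6 mL and the SD is at most half the range, 3 mL. The planned spread of 105.2 − 95.3 = 9.9 mL and the SD of about 10 could not occur. With refills, totals can exceed 150 mL and the SD is unknown.

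**5. How far power depends on the missing SD.** The four planning means average 98.425. Their squared deviations are 9.77, 3.33, 45.90 and 3.33, which sum to 62.33. The SD of the means is √(62.33 / 4) = 3.95, so f = 3.95 / SD. Power at alpha 0.0167, holding the printed differences fixed:

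| Within-group SD | f | 28 per group | 33 per group |
|---|---|---|---|
| 8 (assumed) | 0.493 | 0.98 | 0.995 |
| 10 (printed) | 0.395 | 0.88 | 0.94 |
| 12.7 (assumed) | 0.311 | 0.63 | 0.73 |
| 15 (assumed) | 0.263 | 0.45 | 0.54 |

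This is an illustration and not an estimate. The document gives neither the SD nor the group differences for the 72 h volume. The row for SD 10 also shows that f = 0.448 does not follow from the printed inputs. That is a separate error, and correcting it would leave the present mismatch in place.

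**The case against.** **Power depends on f, not on level.** This is the strongest reply, and it stands. Cohen's f is unit-free and a constant added to every patient's volume does not change it. Going from a 96 mL to a 144 mL background does not by itself alter power. A reader might infer that the trial is underpowered; the documents do not show this, and power could be higher than 0.95. What the difference in level does show is that the planning figures were not measured on this outcome. Whether their SD and differences carry over is then an open question, which the protocol does not address.

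**The figures could fit part of the follow-up.** A reader might infer that the planning values match nothing the trial analyses. That goes too far. With 48 mL of background and up to 48 boluses of 2 mL, each of the 24–48 h and 48–72 h periods can hold 48 to 144 mL, which includes 95 to 105. Table 2 also records PCA usage at 48 h. The conclusion is therefore confined to the 72 h volume.

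**Observed volumes may be lower.** Pumps may be stopped early, or may start before the patient reaches the ward. But bringing 144 mL down to even the highest planning mean needs (144 − 105.2) / 2 = 19.4 h without infusion, on average, and the protocol says that PCA continues for 72 h.

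**The detail may stand in the full protocol or the cited study.** The unit and window of the borrowed figures may well be given there. If this were only a missing label, it would be a small clarification. Here the printed inputs conflict with the printed regimen and outcome, so supplying the label alone would not support 0.95.

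**Conclusion.** The point holds in a limited form. The planning means of 95.3 to 105.2 cannot be 72 h totals in mL under the regimen as written, because background infusion alone gives about 144 mL (142 mL for hours 1–72). They come from another window, unit or regimen, and the document does not show which. A power of 0.95 is therefore unsupported for the 72 h PCA outcome.

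The size of the effect on power cannot be determined from the document: the true value is unknown and is not shown to fall below 0.95. The conclusion that the figures do not match rests only on the stated infusion rate and duration. The stronger statement, that the planned 9.9 mL spread cannot occur at all, holds only if the 150 mL is not refilled. This should be corrected because it is the trial's only power figure and the correction is cheap; it gives no ground for changing the number of patients.

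**What to change.** Keep N = 132. In Sample size:

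1. Withdraw 0.95 as the power for 72 h PCA volume.
2. State the unit and time window of the borrowed means and SD.
3. Restate power at 28 and 33 per group for a PCA measure and window that this trial analyses, over a stated range of SDs and differences for that measure. Subtracting a constant background would not be enough, since it leaves f as it was.
4. Reconcile the Sample size section with Outcomes and with the PCA regimen under Relevant concomitant care, including whether the 150 mL is a limit on the 72 h total. No PCA regimen is proposed here.

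The cost is a rewritten paragraph and a short recalculation, with no added patients or procedures. The downside is that the stated power becomes a range and may be lower than 0.95.

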### Trial design

This will be a single-centre, randomized, prospective, double-blind, superiority clinical trial with four arms. The trial will include three treatment arms where pregabalin will be administered at different doses (25, 50, 75 mg), and one control arm where placebo will be administered. The participants will be equally distributed among the four arms.

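### The planning means show PCA use rising with pregabalin dose and include a 150 mg arm this trial lacks, so the stated power of 0.95 is not supported for the arms studied

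*Protocol article*

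**What the plan says.** The Sample size section of the Protocol article bases the effect size on PCA usage in an earlier three-arm study, "those treated with placebo, pregabalin 75 mg, and pregabalin 150 mg", "with mean values of 95.3, 96.6, and 105.2 respectively, and an approximate standard deviation of 10". To get from three arms to four it adds an invented one: "a fourth hypothetical group was considered with the mean value of 96.6, which is the median value of the three established groups". From these it reports Cohen's f and a G*Power calculation "with a statistical power of 0.95 at an effect size of 0.448 with an alpha level of 0.0167", and "the total sample size needed is found to be 112, and the number of participants needed per group is 28".

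The Trial design section describes "three treatment arms where pregabalin will be administered at different doses (25, 50, 75 mg" plus a placebo arm. The Discussion acknowledges that the earlier study used 75 mg and 150 mg and that this trial works at lower doses. On direction, the Outcomes section says "we plan to check the effects of pregabalin on reduction of postoperative pain and IV PCA usage". The statistical methods section gives the primary objective as comparing different doses of pregabalin with placebo, and plans ANOVA or Kruskal–Wallis followed by Bonferroni comparisons.

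**The concern.** Two things conflict on the face of the text. The sample-size paragraph pairs the means with the arms in sequence, so placebo has the lowest PCA use and 150 mg the highest; a superiority trial seeking a reduction has been planned on data showing an increase. And the four planning means stand for placebo, 75 mg, 150 mg and a hypothetical group, while the trial needs placebo, 25, 50 and 75 mg.

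This paragraph is the only stated basis for the sample size. If the power belongs to a contrast the trial cannot make, a null result for the low doses could be read as coming from a 95%-powered trial when nothing in the plan supports that.

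**Working it through.** **Inputs (Sample size section).** Means 95.3, 96.6, 105.2 and a hypothetical 96.6; SD about 10; f = 0.448; alpha 0.0167; 28 per group, N = 112; 33 per group randomised.

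**Formulas.** f = (population SD of the group means) / (within-group SD). Overall power: noncentral F with 3 and N − 4 degrees of freedom, noncentrality N·f². Pairwise power: two-sided noncentral t with 2n − 2 degrees of freedom, noncentrality (difference/SD)·√(n/2). Alpha is 0.0167 throughout.

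**1. The plan's own figure.** f = 0.448 and N = 112 give noncentrality 112 × 0.448² = 22.5 and power 0.955. So 28 per group reproduces, and 0.95 is the power of the four-group F test. 28/0.85 = 32.9, hence 33 per group.

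**2. The plan's own f.** The means 95.3, 96.6, 96.6, 105.2 average 98.425 and their population SD is 3.947. With SD 10, f = 0.395; noncentrality 112 × 0.395² ≈ 17.5; power 0.88. To obtain 0.448 the SD must be 3.947/0.448 = 8.81. Both SDs are carried forward.

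**3. Printed order (placebo 95.3, 75 mg 96.6, 150 mg 105.2).** Replace the 150 mg mean so that all three doses sit at 96.6. The SD of the means is 0.563, f = 0.056 with SD 10, and overall power is 0.03. A straight line from placebo to 75 mg gives f = 0.048 and power 0.02. For 75 mg versus placebo the difference is 96.6 − 95.3 = 1.3 (0.13 SD, towards more PCA use), with power 0.03 at 28 and at 33 per arm.

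**4. Reversed order (an assumption: placebo 105.2, 75 mg 96.6, 150 mg 95.3).** The outlying mean is now placebo. The documents give no values for 25 and 50 mg, so two assumptions are shown.

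| Means: placebo, 25, 50, 75 mg | f (SD 10) | Overall power, N = 112, SD 10 | Same, SD 8.81 |
|---|---|---|---|
| 105.2, 96.6, 96.6, 96.6 (all doses equal) | 0.372 | 0.83 | 0.92 |
| 105.2, 102.3, 99.5, 96.6 (linear) | 0.320 | 0.66 | 0.80 |

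For 75 mg versus placebo the difference is 105.2 − 96.6 = 8.6:

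| Per arm | SD 10 | SD 8.81 |
|---|---|---|
| 28 | 0.77 | 0.88 |
| 33 (no losses) | 0.85 | 0.93 |

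On the linear assumption with SD 10 and 28 per arm, 50 mg versus placebo (difference 5.73) has power 0.38 and 25 mg versus placebo (difference 2.87) has 0.09.

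**5. Where the shortfall comes from (reversed order, doses equal, SD 10).** Power falls from 0.955 to 0.877 because f does not follow from the stated means and SD, and from 0.877 to 0.826 because the 150 mg mean is dropped. About 0.08 of the 0.13 is the separate error in f; about 0.05 belongs to this point.

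**The case against.** The strongest reply is that the order is a labelling slip. Cohen's f ignores order and direction, so a slip changes neither f nor the sample size, and in the reversed order dropping the 150 mg mean moves f only from 0.395 to 0.372. That stands. A reader might infer that the effect size rests on the 150 mg arm in every case; that is true only of the printed order. The documents cannot settle which order is right.

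A second reply is that the protocol never calls 0.95 the power of a pairwise comparison, and an overall F-test calculation matches the ANOVA planned first. This also stands. A reader might infer that the plan claims 95% power for each dose against placebo; it does not. What remains is that the primary objective is dose against placebo and the calculation uses a Bonferroni alpha, yet no power is given for those comparisons.

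Third, the size depends on an SD given only as approximate and on a dose response the protocol does not state, so single figures such as 77% would be too precise. A favourable pattern can be constructed: in the reversed order, with 25 mg equal to placebo and 50 mg equal to 75 mg, the SD of the means is 4.3, f is 0.43 (SD 10) or 0.488 (SD 8.81), and overall power is 0.93 or 0.98. But that supposes 25 mg does nothing, and the protocol does not assume it. None of these replies removes the contradiction in the text or supplies a justification for the 25 and 50 mg means.

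**Conclusion.** The point holds in this form. As printed, the planning means contradict the expected reduction in PCA use and include a dose the trial does not study. In that order, power for this trial's arms is about 0.03, both overall and for 75 mg versus placebo. If the order is reversed, overall power at N = 112 is 0.83 to 0.92 with all doses equal and 0.66 to 0.80 with a linear dose response; 75 mg versus placebo has 0.77 to 0.88 at 28 per arm. Each range runs from SD 10 to SD 8.81.

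Part of the gap from 0.95 comes from the separate mismatch between f and the stated means. The results rest on alpha 0.0167 as used in the plan; the text's derivation, "the alpha level was set at 0.05 divided by 4, which is 0.0167", is a further inconsistency (0.05/4 = 0.0125) and is left aside here. It would go too far to say the trial is too small: the order of the means depends on a source not available here, and the low-dose means are assumptions.

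**What to change.** 1. Check the cited study and correct which mean belongs to which arm.
2. Rebuild f from placebo, 25, 50 and 75 mg, leaving out the 150 mg mean. State the assumption for 25 and 50 mg, and state an SD that reproduces the reported f.
3. Restate the power, labelled as that of the overall F test.
4. Add power for 75 mg versus placebo as a range. If the reversed order is confirmed, this is 0.77 to 0.88 at 28 per arm and 0.85 to 0.93 at 33. Note that power for 25 and 50 mg is lower unless their effect equals that of 75 mg. If the printed order is confirmed, these data cannot support a planned reduction and another justification is needed.

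The cost is a rewritten paragraph and, very probably, a less favourable stated power. The change itself requires no extra patients and alters neither allocation nor analysis.

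### The sample-size inputs do not follow from the stated data: the means and SD give f = 0.395, not 0.448, and 0.05/4 is 0.0125, not 0.0167, so 28 per group gives about 85–88% power, not 95%

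*Protocol article*

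**What the plan says.** All the inputs are in the Sample size section of the protocol article. A previous three-arm study of placebo, pregabalin 75 mg and pregabalin 150 mg supplies PCA usage "with mean values of 95.3, 96.6, and 105.2 respectively, and an approximate standard deviation of 10". Because this trial has four arms, "a fourth hypothetical group was considered with the mean value of 96.6". From these figures Cohen's f "was calculated, resulting in an effect size of 0.448". For the Bonferroni correction, "the alpha level was set at 0.05 divided by 4, which is 0.0167". The calculation itself is described thus: "the software G*Power 3.1.9.7 was used with a statistical power of 0.95 at an effect size of 0.448 with an alpha level of 0.0167". The result is that "the total sample size needed is found to be 112, and the number of participants needed per group is 28", raised to 33 per group (132 in total) for about 15% loss.

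The Statistical methods section gives the primary objective as comparing the pregabalin doses with placebo. It plans an ANOVA (or Kruskal–Wallis) with Bonferroni-adjusted comparisons, and takes P < 0.05 as significant in all analyses.

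**The concern.** Two statements can be checked with a calculator, and both fail. The effect size does not follow from the means and SD printed beside it, and the alpha is not the quotient it is said to be. Both errors raise the apparent power.

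There is also a mismatch of test and question. A Bonferroni level meant for pairwise comparisons was entered into an omnibus F-test calculation. The resulting power is therefore not the power of any dose-versus-placebo comparison, although those comparisons are the stated objective. Nor does a divisor of 4 match a natural family of comparisons: four arms give three comparisons with placebo (0.05/3 = 0.0167) or six pairs (0.05/6 = 0.0083).

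This is the trial's only justification of its size. If the result is null, a reader relying on 95% power would give it more weight than the design supports.

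**Working it through.** **Inputs (Sample size section).** Means 95.3, 96.6, 96.6 (hypothetical fourth group) and 105.2; SD about 10; 28 evaluable per group, N = 112; target power 0.95; stated f = 0.448; stated alpha 0.0167.

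**Method.** One-way ANOVA F test with k = 4: numerator df 3, denominator df N − 4 = 108, noncentrality λ = N × f². Power is the probability that a noncentral F exceeds the central-F critical value at the chosen alpha. Cohen's f is the SD of the group means (divisor k) over the within-group SD.

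**1. The plan's own figure.** With f = 0.448, λ = 112 × 0.448² = 22.48. At alpha 0.0167, power is 0.955 and 28 is the smallest group size reaching 0.95. Then 28/0.85 = 32.9, rounded up to 33. The calculation reproduces, which identifies the test used.

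**2. Effect size from the stated means.**
- Grand mean: (95.3 + 96.6 + 96.6 + 105.2)/4 = 98.425
- Squared deviations: 9.77, 3.33, 3.33, 45.90; mean 15.58; square root 3.947
- f = 3.947/10 = **0.395**

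Other ways of forming f do not give 0.448 either:

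| Variant (SD 10) | f |
|---|---|
| Original three groups only | 0.439 |
| Four groups, divisor k − 1 | 0.456 |
| Fourth group at the mean of the three | 0.380 |
| Fourth group at 95.3 | 0.413 |
| Fourth group at 105.2 | 0.465 |

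With the four stated means, 0.448 needs an SD of 3.947/0.448 = 8.81.

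**3. Alpha.** 0.05/4 = **0.0125**; 0.05/3 = 0.0167; 0.05/6 = 0.0083.

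**4. Power at 28 per group, and group size for 95% power.** With f = 0.395, λ = 112 × 0.1558 = 17.45.

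| f | alpha | Power, 28 per group | n per group for 0.95 |
|---|---|---|---|
| 0.448 | 0.0167 | 0.955 | 28 |
| 0.448 | 0.0125 | 0.944 | 29 |
| 0.395 | 0.0167 | 0.877 | 35 |
| 0.395 | 0.0125 | 0.854 | 37 |
| 0.395 | 0.0083 | 0.82 | 39 |

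Correcting alpha alone costs about 1 point of power; correcting f alone costs about 8.

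**5. Pairwise comparisons.** Two-sample t test, 28 per group, SD 10. The largest placebo contrast in the stated means is 105.2 − 95.3 = 9.9 (d = 0.99). Its power is 0.89 at alpha 0.0167 and 0.86 at 0.0125. In the order printed, 105.2 is the 150 mg group, a dose not studied here. The only shared dose, 75 mg, differs from placebo by 96.6 − 95.3 = 1.3 (d = 0.13), with power of about 0.03 at alpha 0.0167.

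**The case against.** The case for leaving the figure alone has five parts.

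- **The divisor is only a slip.** The value 0.0167 appears twice, once as the software input, and three comparisons with placebo give 0.05/3. This is a plausible reading, and it makes 0.88 the better single figure than 0.85. It does not restore 0.95, because the effect-size error remains.
- **The SD is approximate.** The authors may have used unrounded or group-specific SDs from a source not available here. But any SD that rounds to 10 (9.5 to 10.5) gives f from 0.416 down to 0.376. Power is then 0.91 to 0.83 at alpha 0.0167, or 0.90 to 0.81 at 0.0125. The 8.81 needed is not in the document and would not round to 10.
- **33 per group are randomised.** If all 33 were analysed, power at SD 10 would be 0.935 (alpha 0.0167) or 0.920 (0.0125), still below 0.95. The section on non-adherence and missing data excludes patients who drop out or have missing data, and expects 20% withdrawal. That leaves about 33 × 0.80 = 26 per group, with power of 0.84 or 0.82.
- **The omnibus test may be run at 0.05.** Read literally, the Statistical methods section allows this, and power with f = 0.395 is then 0.946, close to the claim. This is the strongest point. However, the Sample size section ties its power to alpha 0.0167, so the statement as written remains wrong, and an omnibus test at 0.05 does not give the power of the placebo comparisons.
- **A corrected f still borrows from a 150 mg arm.** This is true, and it is a reason to report the power of this trial's own contrasts. It does not defend 0.448.

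**Conclusion.** The concern holds. The printed means and SD give f = 0.395, and 0.05/4 is 0.0125. On the plan's own test at 28 evaluable per group, power is 0.854 at alpha 0.0125 or 0.877 at alpha 0.0167, against the stated 0.95. The chance of missing the assumed effect is 12–15%, more than double the 5% implied. The effect-size error accounts for most of the gap.

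These figures assume SD 10, equal groups, and the four-group F test that the plan's own result identifies. No SD that rounds to 10 brings power at 28 per group above about 0.91 at either alpha. The document does not show whether the divisor 4 or the value 0.0167 was intended, and the conclusion does not depend on which.

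**What to change.** Keep N = 132 and correct the Sample size section:

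1. Replace f = 0.448 with 0.395. If a more exact SD from the previous study was used, print that SD and the f that follows from it.
2. State alpha as 0.05/3 = 0.0167 for three comparisons with placebo, or 0.05/6 = 0.0083 if all pairs are intended, and remove the statement that 0.05/4 is 0.0167.
3. Restate power at 28 evaluable per group as 0.88 at alpha 0.0167 (0.85 at 0.0125; 0.82 if 0.0083 is chosen).
4. Say that this is the power of the omnibus F test, and add the power of the dose-versus-placebo contrasts that will be reported, with the difference assumed for each dose in this trial. The 9.9 difference should not stand in for them without comment, since as printed it belongs to a dose outside the trial.

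The cost is a text correction and a less favourable stated power. No patients are added and no analysis changes. Holding to 95% power instead would need 35 evaluable per group at alpha 0.0167 (42 randomised per group, 168 in total, at 15% loss) or 37 at 0.0125 (44 per group, 176 in total).
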